## Abstract

**Background:**

To describe the rationale and design of a future study comparing results of plate fixation and Elastic Stable Intramedullary Nailing (ESIN) with a Titanium Elastic Nail (TEN) for adults with a dislocated midshaft clavicular fracture.

**Methods/Design:**

Prospective randomized multicenter clinical trial in two level 1 and one level 2 trauma centers. 120 patients between 18 and 65 years of age will be included. They are randomized to either plate fixation or ESIN with a TEN with a one year follow-up. Sixty patients will be treated with plate fixation and 60 patients will be treated with ESIN. Primary outcome parameter is the Disabilities of the Arm, Shoulder and Hand score after 6 months. Secondary outcome parameters are Constant Shoulder Score, complications, experienced pain, radiologic consolidation and cosmetics after both procedures.

**Discussion:**

Prospective randomized studies comparing operative techniques for treatment of dislocated midshaft clavicular fracture are lacking. By studying shoulder function, complications, quality of life, radiographic union, cosmetics as well as experienced pain, a complete efficacy assessment of both procedures will be performed.

**Trial registration:**

The POP study is registered in the Dutch Trial Register (NTR NTR2438).

## Background

Clavicular fractures in adults occur commonly and account for approximately 5% of all fractures. Around 80% of the clavicular fractures involve the midshaft and over half of these fractures are dislocated [1,2]. Historically, clavicular fractures were treated conservatively, mostly with sling or figure-of-eight bandage [3,4]. Consolidation was achieved within a few weeks, even with severe dislocation.

Recently, poor results were described of conservatively treated dislocated midshaft clavicular fractures (DMCF) [5-10]. The number of nonunions after conservative treatment appeared to be much higher than previously assumed [5]. Furthermore, the clinical importance of clavicular malunion was discovered with symptoms like persistent pain, permanent loss of strength, rapid fatigability of the shoulder joint and disappointing cosmetic results [6-8]. Altogether these symptoms result in decreased patient satisfaction scores after conservatively treated DMCF [9,10].

Two commonly used operative techniques for treatment of DMCF are plate fixation and Elastic Stable Intramedullary Nailing (ESIN) [11]. In recently reported prospective randomized studies, functional results after both techniques proved to be superior compared to conservative treatment of DMCF [12,13]. Furthermore, a recent meta-analysis demonstrated a significantly lower nonunion rate after surgical treatment in general [8].

Prospective randomized studies comparing operative techniques for treatment of DMCF are lacking [14]. The aim of this article is to describe the rationale and design of a prospective randomized study comparing results of plate fixation and ESIN with a Titanium Elastic Nail (TEN).

## Methods and Design

### Study design

Prospective randomized multicenter study involving three hospitals in The Netherlands, including Diakonessenhuis, Utrecht (level 2 traumacenter); Medisch Centrum Haaglanden, The Hague and St. Elisabeth Hospital, Tilburg (both level 1 traumacenters). Patients with DMCF, defined as at least one shaft width difference in height between the fracture parts regardless of the reduction, are allocated to either plate fixation or intramedullary fixation with ESIN through randomization. A flow chart of the study is shown in Figure 1.

**Figure 1 F1:**
[figure not shown]
**Flowchart of POP-study**.

### Patient population

A total number of 120 patients will be included in the trial (see sample size considerations).

Patients will be recruited at the emergency room (ER) of the participating hospitals. Patients are screened for eligibility according to the criteria listed in table 1. Patients with a DMCF on one side and no contraindications for general anesthesia are eligible for inclusion in the study.

**Table 1 T1:** Inclusion and exclusion criteria

Inclusion criteria	Exclusion criteria
-Unilateral dislocated midshaft clavicular fracture	-Age < 18 years or > 65 years
-No medical contraindications to general anaesthesia	-Multitrauma patients
-Provided informed consent	-Open fracture
	-Pathological fracture
	-Fracture > 1 month old
	-Neurovascular disorders
	-Glasgow Coma Scale <12 (moderate to severe head injury)
	-Inability to comply with follow-up (for example due to an inability to read or complete forms)
	-Pre-existing shoulder pathology in affected side (rotator cuff lesion, acromioclavicular pathology or previous shoulder surgery)

### Intake

Ultimately within 1 week, an appointment with an orthopedic trauma surgeon and the investigator will take place. If informed consent is obtained, the patient is included in the study, patient data are obtained by the investigator (table 2) and the patient is randomized.

**Table 2 T2:** Preoperative data

Preoperative data	
- Age	- Smoking
- Gender	- Medical history
- Dominant arm	- Medication
- Trauma mechanism (sports, traffic accident, etc)	- SF-36 Questionnaire [18]
- Sports (if yes; at what level? Recreational or professional)	- Body Mass Index
- Occupation	- AO Classification of fracture *

* this classification exactly concurs to the OTA classification of midshaft clavicular fractures

### Randomization

Patients are randomized prior to surgery in the doctor's office by computerized block randomization for either plate fixation or ESIN. The block varies between 2, 4, 6 and 8 patients. In each block the two operative techniques are equally represented. This randomization procedure will be stratified by participating hospital. After randomization, follow-up of patients will take place according to the intention-to-treat principle.

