### End Points

The primary endpoint is the DASH score 6 months after surgery. Secondary endpoints are listed in table 4.

**Table 4 T4:** Primary and secondary endpoints

Primary Endpoint	Secondary Endpoints
- DASH score after 6 months	- Constant Score after 6 months
	- DASH and Constant Score after 6 weeks, 3 months and 1 year
	- Complications: intra-operative, post-operative period (2 weeks) and after 6 weeks, 3 and 6 months and 1 year
	- Reoperation after unsatisfying result in a time horizon of 1 year (including implant removal)
	- Time to radiological consolidation, with a maximum time horizon of 6 months
	- Pain score, until 2 weeks postoperative
	- Cosmetic satisfaction after 6 months and 1 year

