### Statistical Methods

Data will be analyzed according to the intention-to-treat principle. The difference between the operative techniques at the end of the follow-up period in DASH (primary outcome) and Constant scores will be tested for significance using the Student's T-test or the Mann-Whitney U test, depending data distributions. A general linear random effects model will be applied to assess differences during the follow-up period in DASH, Constant, pain, and SF-36 scores to account for repeated measures within patients. The difference in the frequency of complications during follow-up will be assessed with Poisson regression, whereas the Chi-square test or Fisher's exact test will be used to test for differences in proportion of re-operated patients. Differences in cosmetic satisfaction will be tested using the Mann-Whitney U-test. Time to radiological consolidation will be assessed by Kaplan-Meier analysis. A p-value of < 0.05 will be considered statistically significant in all analyses. SPSS software will be used for statistical analysis.

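### Randomisation is stratified by hospital but the primary DASH test is not; if hospital is prognostic, the test is mildly conservative and gives up a little power

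*Protocol article*

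**What the plan says.** The protocol article, under Study design, describes the trial as "Prospective randomized multicenter study involving three hospitals in The Netherlands". Under Randomization it uses computerised blocks of 2, 4, 6 or 8 patients and states "In each block the two operative techniques are equally represented" and "This randomization procedure will be stratified by participating hospital". Arms are therefore balanced within each hospital, apart from an unfinished last block.

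End Points states "The primary endpoint is the DASH score 6 months after surgery". Statistical Methods says that the difference in DASH, labelled there as the primary outcome, "will be tested for significance using the Student's T-test or the Mann-Whitney U test, depending data distributions". That sentence places the comparison at the end of follow-up rather than at 6 months; the present point is the same for either time.

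A random effects model is listed separately for DASH, Constant, pain and SF-36 over follow-up. Its stated purpose is "to account for repeated measures within patients"; hospital is not mentioned. Table 2, under Intake, lists data collected before randomisation, among them SF-36 and "AO Classification of fracture". No baseline DASH is listed.

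**The concern.** Stratified, blocked allocation balances hospital between the arms, so differences between hospitals cancel out of the treatment contrast. A two-sample t-test does not know this. It leaves the between-hospital variance in its error term and reports a standard error larger than the true sampling variability of the estimate. The confidence interval is then too wide and the test rejects less often than it should. The rank test works by the same mechanism.

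This cannot simply be left to a later analysis plan. The protocol article is not silent: it names a primary test that cannot carry the stratification factor, so an adjusted analysis would depart from the published text. At stake is some precision that the design has already secured.

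**Working it through.** **Inputs.** From Sample Size and Power: difference 6 points, SD 11, two-sided alpha 0.05, power 0.80, 53 per arm. From Randomization and Study design: 1:1 allocation within three hospitals. Assumed, because the documents give no value: R², the share of total DASH variance explained by hospital, taken as 0, 2%, 5%, 10% and 15%. The SD of 11 is read as the overall SD.

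**The plan's own figure.** n per arm = 2 × [11 × (1.960 + 0.842) / 6]² = 52.8, so 53. Power at 53 per arm is 80.2% (normal approximation). Then 106 / 0.9 = 118. With an assumed O'Brien-Fleming inflation of about 1.008 it is 107 / 0.9 = 119, and 120 is the next even total. The plan's figures reproduce, and they are for an unadjusted comparison.

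**Effect of ignoring hospital.**
- SE reported by the t-test: 11 × √(2/53) = 2.137.
- True SE under balance within hospital: 2.137 × √(1 − R²). A model with hospital reports this value.
- Type I error of the t-test: 2 × [1 − Φ(1.96 / √(1 − R²))].
- Power, unadjusted: Φ[(6/2.137 − 1.96) / √(1 − R²)].
- Power, adjusted: Φ[6 / (2.137 × √(1 − R²)) − 1.96].

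| Assumed R² | True SE | Type I error, t-test | Power, unadjusted | Power, with hospital | Points forgone |
|---|---|---|---|---|---|
| 0 | 2.137 | 5.0% | 80.2% | 80.2% | 0 |
| 2% | 2.115 | 4.8% | 80.4% | 81.0% | 0.6 |
| 5% | 2.083 | 4.4% | 80.8% | 82.1% | 1.4 |
| 10% | 2.027 | 3.9% | 81.4% | 84.1% | 2.7 |
| 15% | 1.970 | 3.4% | 82.1% | 86.1% | 4.0 |

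The last column is taken from unrounded powers.

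**Check by simulation** (three hospitals of 36, the protocol's block sizes, 6,000 trials per setting; Monte Carlo error about 0.3 points for type I error and 0.5 for power). At R² 5%, type I error is 4.4%, and power is 81.1% unadjusted against 82.5% with hospital. At 10%, type I error is 3.8 to 3.9%, and power is about 81% against 84%; the t-test reports a mean SE of 2.11 to 2.12 while the estimate's actual SD is 1.97 to 2.02. At R² of 0 the two analyses agree. The Mann-Whitney test was not simulated, so these sizes are for the t-test.

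**What the assumed R² means in DASH points.** For three equal hospitals with equally spaced means, the range between the outer two is 2 × √(1.5 × R² × 121). That is 3.8, 6.0, 8.5 and 10.4 points at R² of 2%, 5%, 10% and 15%.

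**The case against.** The strongest reply is that the harm is assumed. An R² of 5% already needs hospitals about 6 points apart, which is the trial's own clinically relevant margin. The document gives reasons to expect less: one set of eligibility criteria (Table 1), surgeons with over 20 procedures in each technique (Safety measures), a self-completed questionnaire (Follow-up) and one investigator at all visits (Discussion). Trauma-centre level and start date differ between hospitals, but nothing shows that either affects DASH. At 2% the cost is negligible. This stands, and it is why the loss must be stated conditionally and why values near zero belong in the range.

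A reader might infer that the trial is underpowered. The documents do not support that. The sample size was computed for an unadjusted test, and with 11 as the overall SD that test keeps 80% or more. The loss is measured only against the better analysis.

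A reader might also infer that leaving out the Table 2 variables is an error of the same kind. It is not. The too-wide standard error arises only for the factor that the allocation balances. For other baseline variables the unadjusted standard error is valid, merely less efficient. The documents do not show fracture class to be prognostic for DASH. Nor can one say that the baseline data go unused: the pre-operative SF-36 may enter the repeated-measures model for SF-36, since the text does not settle it.

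What remains is the mismatch between a stratified design and a named unstratified primary test.

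**Conclusion.** The point holds as a modest, conditional loss of efficiency. If hospital explains 2% to 15% of DASH variance, the t-test's true level is about 4.8% to 3.4%, and about 0.6 to 4 percentage points of power are forgone. If it explains nothing, there is no cost. The trial's validity is not in question, because the error is on the conservative side. The conclusion rests on near-balance within hospitals, which the blocking provides, on 11 being the overall SD, and on an R² that has to be assumed. It deserves a change because the remedy is nearly free and is best settled before outcome data are seen.

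**What to change.** - Make the primary DASH analysis a linear model with treatment and hospital (three levels, fixed effect).
- Where the plan now falls back on Mann-Whitney for non-normal data, use a rank test stratified by hospital (van Elteren), so that the fallback also respects the design.
- Include hospital in the random effects models for DASH, Constant, pain and SF-36.
- For complications and re-operation, use hospital terms or strata only where event counts allow; sparse events across three hospitals may not support them.
- Optionally, pre-specify a few baseline variables from Table 2, such as AO class, as covariates. This may add efficiency but corrects no error.

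The cost is two degrees of freedom in the primary model and a change of wording. No new data are needed, and the sample size can stay as it is.

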### Interventions

After randomization the patient will be scheduled for surgery as soon as possible but ultimately 4 weeks after the initial trauma.

#### Operative procedure plate fixation

Patients are administered prophylactic antibiotics. With general anaesthesia, the patient is positioned in a beach-chair semi-sitting position. The involved shoulder is prepared and draped, and an incision is made just under the fracture site. If possible, supra-clavicular nerves are identified and spared. The fracture site is identified. In simple fractures, the fracture is reduced and a small fragment, low contact compression plate is fixed upon the anterosuperior surface of the bone starting medially using bicortical, non-angular stable screws. On the outer sides of the plate angular-stable screws are placed. In oblique or complex fractures interfragmentary lag screws can be placed to obtain compression. In case of severe comminution only bridging plate is performed. The fascia and the skin are closed in layers.

#### Operative procedure ESIN using a TEN

Patients are administered prophylactic antibiotics. With a general anesthetic, the patient is placed in supine position. A small skin incision is made approximately 1 centimeter lateral to the sternoclavicular joint. The anterior cortex is opened with a sharp pointed reamer while care is being taken to not accidentally perforate the thorax. A TEN is inserted (the diameter varies from 2 to 3,5 mm, dependent on the width of the bone). Closed reduction, eventually supplemented with two percutaneously introduced pointed reduction clamps, is performed under fluoroscopic control. If closed reduction fails, an additional incision will be made above the fracture site for direct manipulation of the main fragments. After complete introduction of the TEN in the lateral fragment, the fracture is compressed and the TEN will be cut as short as possible at the medial end. The fascia and the skin are closed in layers.

### Postoperative management

If possible, surgery is performed as a day case. Postoperatively, patients are given a sling but are encouraged to start with pain-dependent mobilisation immediately and to discard the sling as soon as possible. Load bearing is not recommended before osseous consolidation. Patients are advised to take pain medication when necessary. The type and amount of analgesics should be kept in the pain diary.

### Follow-up

The patient is requested to record - on a daily basis during the fortnight immediately following surgery - the pain experienced as well as the type and amount of analgesics used. Experienced pain is assessed with a 10-point Likert scale (0 = no pain and 10 = extremely painful).

All patients are reviewed in the outpatient department by the treating surgeon and investigator at 2 and 6 weeks, 3 and 6 months and 1 year after surgery. All visits include standardized clinical evaluation and registration of possible complications by the treating surgeon and the investigator (table 3).

**Table 3 T3:** Complications

Intra-operative complications	Post-operative complications
- Nerve/vessel damage	- Wound healing disorders (infection, hypertrophic scar, dehiscence)
- Other operative complications	- Transient brachial plexus laesion (defined as paresthesia of the arm, and weakness of the pink and index finger)
	- Irritation of the implant (post-operative pain/itch/redness/irritation)
	- Migration of the implant
	- Breakage of the implant
	- Non-union (defined as lack of radiographic healing with clinical evidence of pain and motion at the fracture site after 6 months)
	- Mal-union (defined as union of the fracture in a shortened, angulated, or displaced position with weakness, easy fatigability, pain with overhead activity, neurologic symptoms, and shoulder asymmetry)
	- Other complications

At the 2 weeks outpatient visit the pain diary is discussed by the researcher with the patient. Radiographs will be taken in order to check implant position and, at subsequent follow-up visits until radiographic union. Radiographic union is defined as complete cortical bridging between proximal and distal fragments on both radiographs as determined by the treating surgeon.

The Disabilities of the Arm, Shoulder and Hand (DASH) and Constant scores will be gathered at the 6 weeks, 3 and 6 months and 1 year postoperative visits by the investigator [15-17].

The DASH questionnaire is a self administered region-specific outcome instrument developed as a measure of self-rated upper extremity disability and symptoms. The DASH questionnaire consists mainly of a 30-item disability/symptom scale, scored 0 (no disability) to 100 (= completely disabled upper extremity) [15,16]. To prevent bias, the DASH questionnaires will be completed in absence of the operating surgeon, before the clinical assessment.

The Constant score includes an analysis of pain, shoulder motion, strength, and function. From a perfect score of 100, it reserves 35 points for patient-reported subjective assessment, including the presence of pain and the ability to perform basic activities of daily living, and 65 points for objective measurement. For the latter, 40 points are allocated to range of motion and 25 points are allocated to strength [17].

The cosmetic result after 6 weeks, 3 and 6 months, and 1 year is assessed by eliciting a patient satisfaction score on a 0 (= very unsatisfactory) to 10 (= very satisfactory) Likert scale.

After 6 months and 1 year the patient is asked to complete the SF 36 questionnaire again (see table 2) [18]. The SF 36 is a validated questionnaire designed to measure health related quality of life.

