The main goal of this study is to compare two principles of osteosynthesis: plate fixation and ESIN. Therefore the operating surgeon is free in his choice of plate regarding compression or angular stable locking. The operating surgeon is also free to decide the location of the plate, both superior and anterior/inferior plating are allowed. If plate fixation proves to be superior, a following study should be initiated to compare different methods of plate fixation.

There are some limitations of this study. Due to different incisions blinding is not possible. However, by using a self administered outcome instrument, the investigator-related bias is minimised for the primary endpoint. In this study the DASH score is used as primary endpoint. The DASH score does not specifically focus on clavicular function. However, a score which solely assesses clavicular function is lacking. In our opinion the DASH score provides the most reliable result for rating upper extremity disability and symptoms. To provide a complete overview of shoulder function the Constant score is used as a secondary endpoint.

A limitation of multicenter studies in general is that patient follow-up is often performed by multiple doctors resulting in decreased consistency of the clinical evaluation (interobserver bias) and increased loss to follow-up. In this study the same investigator ([name]) will be present during all patient visits at the outpatient department. Therefore, the consistency of the results will be improved and loss to follow-up rates should be reduced.

This prospective randomised multicenter study is designed to compare plate fixation and ESIN with a TEN for DMCF. As shoulder function, complications, quality of life, radiographic union, cosmetics and experienced pain are assessed, this study will provide a complete efficacy assessment of both procedures.

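### Radiographic union is decided by the unblinded treating surgeon, although the one investigator relied on for consistent follow-up is present at every visit

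*Protocol article*

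**What the plan says.** All references are to the protocol article.

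- **Follow-up** defines union as "complete cortical bridging between proximal and distal fragments on both radiographs as determined by the treating surgeon". It names no second, independent or consensus reader. Radiographs continue at successive visits only until union is reached.
- **Follow-up** also sets out who attends: "All patients are reviewed in the outpatient department by the treating surgeon and investigator at 2 and 6 weeks", and then at 3 months, 6 months and 1 year. Complications, including non-union, are registered by the two together.
- **Follow-up** protects the primary outcome from the surgeon's influence: "the DASH questionnaires will be completed in absence of the operating surgeon, before the clinical assessment".
- **End Points (Table 4)** lists as a secondary endpoint "Time to radiological consolidation, with a maximum time horizon of 6 months". **Statistical Methods** assigns it a Kaplan-Meier analysis.
- **Discussion** states "Due to different incisions blinding is not possible", and says that, because the DASH is self-administered, "the investigator-related bias is minimised for the primary endpoint". On multicentre trials it observes that "patient follow-up is often performed by multiple doctors resulting in decreased consistency of the clinical evaluation (interobserver bias") and answers that one and the same investigator "will be present during all patient visits at the outpatient department".

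**The concern.** Union is a judgement made on a film by someone who knows the allocation. The plan gives that judgement to a reader who changes from patient to patient across three hospitals and who has a stake in the result if, as seems likely, that reader did the fixation.

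The authors take care over this kind of problem elsewhere. They keep the operating surgeon out of the room while the patient fills in the DASH, and they use a common investigator to make follow-up more uniform. Neither safeguard reaches the union reading.

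At stake is the credibility of time to consolidation. Varying thresholds between readers add noise. A preference for one technique would add bias, and the Discussion itself offers a directional expectation: closed nailing leaves the fracture haematoma intact and might speed healing. A lenient call also ends the film series, so a later re-reading cannot recover the date on which a stricter reader would have called union.

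**Working it through.** The point rests on no figure in the plan, so the main check is to set the passages side by side.

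**1. Who reads, and who is available.** Follow-up assigns the union decision to the treating surgeon. Follow-up and the Discussion both place the investigator at the same visits. The staff for a common reading are therefore already there.

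**2. Is the treating surgeon the operating surgeon?** The text does not say so. Follow-up uses both terms. Keeping the operating surgeon away while the DASH is completed makes most sense if that surgeon normally attends the visit, so the identity is probable but remains an inference.

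**3. Which outcomes depend on the reading.**
- Time to consolidation depends on it wholly.
- Non-union depends on it in part. Table 3 also requires clinical pain and motion at the fracture site after 6 months, and registration is joint.
- The DASH does not depend on it.

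**4. How far one call moves the endpoint.** Taking 3 months as about 13 weeks and 6 months as about 26 weeks, a call moved by one visit shifts the recorded date by 13 − 6 = 7 weeks or 26 − 13 = 13 weeks.

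**5. Sample size, for completeness.** With a difference of 6, SD 11, two-sided alpha 0.05 and power 0.80, n per arm = 2 × [11 × (1.960 + 0.842) / 6]² = 52.8, so 53, as stated. The reader of the films does not enter this calculation.

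**6. Illustrations on assumed inputs.** The article gives no union rates and no reader-agreement data. Every union rate, error rate and shift below is an assumption. The number per arm is 120 × 0.9 / 2 = 54. The test is a two-proportion normal approximation at a single visit, two-sided 0.05, which is not the planned Kaplan-Meier analysis.

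*Symmetric misreading.* The observed proportion is p(1 − e) + (1 − p)e, with true union assumed at 60% and 80%.

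| Error rate e | Observed proportions | Difference | Power |
|---|---|---|---|
| 0 | 60% v 80% | 20 points | 62% |
| 10% | 58% v 74% | 16 points | 42% |
| 15% | 57% v 71% | 14 points | 33% |

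This is the cost of misreading in general. It is not the gain from changing the reader, because the investigator would misread some films too.

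*Arm-dependent reading.* Assume no true difference, and readings in one arm shifted upwards from a true union proportion of 0.50, 0.70 or 0.85. The chance of a significant result in the favoured direction, nominally 2.5%, becomes:
- 5-point shift: 7.5%, 8.4% and 11.9%
- 10-point shift: 17.9%, 22.2% and 40.9%

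Nothing in the article says whether such a shift exists, or that a different unblinded reader would be free of it.

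**The case against.** The case for leaving the plan alone has substance.

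- **No evidence of a better reader.** Nothing shows that the investigator reads films more accurately than a trauma surgeon. This stands, and it is why the power figures cannot be credited to the change.
- **Masking is not achieved.** Plate and nail are visible to any reader. A single reader with a preference would push all readings one way, whereas preferences among several surgeons might partly cancel. This stands as a limit on the remedy. What the change removes is variation between readers and, probably, surgeons judging their own work.
- **Existing protections.** Randomisation is stratified by hospital, surgeons are expected to have done more than 20 procedures in each technique, and the bridging criterion is explicit. These should turn most between-reader variation into noise. They do not address unblinded self-assessment.
- **A simple swap of readers would fail.** Both readers attend the same visit, and films stop at union. If the surgeon's reading ends the series, it can censor the investigator's endpoint. This is right, and the fix has to deal with it.

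A reader might also infer that the Discussion and Follow-up contradict each other. They do not: the Discussion speaks of clinical evaluation, claims only that consistency will improve, and makes no statement about who reads films.

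**Conclusion.** The concern holds in a limited form and at low severity. The plan gives an unblinded, varying reader sole charge of the reading that determines one listed secondary endpoint and part of the non-union definition, while the person used elsewhere to secure consistency is present and not used for it.

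Three stronger conclusions are tempting and are not supported:
- That surgeons are stated to judge their own fixation. The text says treating surgeon, and the rest is inference.
- That non-union is as exposed as time to consolidation. It also needs clinical signs and is registered jointly.
- That a known amount of power is lost or a known bias introduced. Without reader-agreement figures the size cannot be derived, and the illustrations depend on their assumptions.

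The self-administered DASH at 6 months and the sample size are untouched.

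**What to change.** For the study endpoint, amend the definition in Follow-up as follows:

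1. The common investigator reads every study film against the existing cortical-bridging definition and records the result at the visit, before the treating surgeon's reading is known.
2. That reading is used for time to radiological consolidation.
3. The treating surgeon's reading continues to serve patient care, is recorded as a secondary reading, and agreement between the two is reported.
4. The protocol states which reading ends the study film series, in such a way that a discordant reading by the surgeon does not censor the endpoint.

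**Cost.** Some reading and recording time for an investigator who already attends, and possibly one further film at an already scheduled visit when the readings differ. No extra visit or staff is needed. The remaining weakness, a reader who sees the implant and may have a preference, should be acknowledged among the limitations.
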